**Methods:**

Three centers (Centre de recherche de l’Institut universitaire de cardiologie et de pneumologie de Québec in Québec, Groupement des Hôpitaux de l’Institut Catholique de Lille in France, and FormAction Santé in France) will be involved in this multinational project, which is divided into 2 studies. For study 1 (objective 1), 30 participants (Québec, n=15; France, n=15) will be recruited. Two laboratory visits will be performed to assess anthropometric data, pulmonary function, and the 3 exercise tolerance tests (CPET, 6MWT, and 6MST). Concurrent validity (paired sample t tests and Pearson correlations) and agreement (Bland-Altman plots with 95% agreement limits) will be evaluated. For study 2 (objectives 2 and 3), 52 participants (Québec, n=26; France, n=26) will be recruited. Following a familiarization trial (trial 1), the 6MST will be conducted on 2 separate occasions (trials 2 and 3), once under direct supervision and once under remote supervision, in a randomized order. Paired sample t test, Bland-Altman plots, and intraclass correlations will be used to compare trials 2 and 3. A semistructured interview will be conducted after the third trial to collect participants’ perspectives.

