In individuals with COPD, initial studies indicate that the 6MST is reliable, as no significant difference in test results was found when repeated on consecutive days in a laboratory setting [16]. The 6MST is also valid, as the number of steps taken during the test is correlated with the total distance traveled during the 6MWT (*r*=0.56-0.87, *P*<.01), peak power during CPET (*r*=0.46, *P*<.01), and peak oxygen consumption during CPET (*r*=0.39, *P*<.01) [17,18]. Responsiveness to change following pulmonary rehabilitation has also been shown, with a minimally important difference estimated at 40 steps [19]. Finally, predictive equations have been computed to individualize aerobic training intensity using the 6MST [20]. However, to our knowledge, cardiorespiratory responses during the 6MST in individuals with COPD have not been formally compared with those during the 6MWT and CPET to date. This is particularly important when considering the development of home-based and telerehabilitation programs, as different cardiorespiratory responses to testing may elicit safety concerns. In individuals with ILD, there is limited evidence regarding the validity of the 6MST, as the number of steps taken during the test is correlated with the total distance traveled during the 6MWT (*r*=0.70, *P*<.01) [21]. Interestingly, in individuals with ILD, cardiorespiratory responses during the 6MST have been compared with the 6MWT. In this population, the 6MST leads to greater heart rate and ventilatory responses, and blood oxygen saturation remains higher during the 6MST [21,22]. Finally, as the 6MST has only been validated in laboratory or hospital settings, metrological properties in home-based settings with direct or remote (ie, videoconferencing) monitoring are currently unknown in individuals with COPD or ILD.

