### Objectives and Hypotheses

#### Overview

The overall aim of this project is to provide further evidence regarding the metrological properties of the 6MST in individuals with COPD or ILD. Specific objectives and hypotheses are described below.

#### Objective 1

Objective 1 is to determine concurrent validity and the level of agreement (or bias) between peak cardiorespiratory responses and reported symptomology during the 6MST and CPET and the 6MST and 6MWT. The corresponding hypotheses are that peak cardiorespiratory responses and reported symptomology to the 6MST will be strongly correlated to those measured during CPET and the 6MWT (ie, concurrent validity), and that these values will be systematically lower than those measured during CPET (ie, presence of bias), but similar to those measured during the 6MWT (ie, no bias).

#### Objective 2

Objective 2 is to determine test-retest reliability for the 6MST in home-based settings under direct and remote (ie, videoconferencing) monitoring. The corresponding hypothesis is that measurement error will be minimal and intraclass correlations will be good and similar between direct and remote supervision.

#### Objective 3

Objective 3 is to determine the safety and the perception of the 6MST in individuals with chronic pulmonary diseases in home-based settings under direct and remote monitoring by collecting adverse events and qualitative feedback. The corresponding hypothesis is that the test will be safe (ie, absence of serious adverse events) and individuals will report a good level of overall satisfaction with the test, irrespective of the type of supervision.

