#### Second and Third Trials

The second and third trials of the 6MST will be performed in a randomized order, with either direct (therapist present at the home) or remote (therapist present through videoconferencing software, as in a telerehabilitation setting) monitoring. For the remotely monitored trial, another person (ie, family member, etc) will be present to ensure safety in case of emergency. The 6MST and adverse events will be, respectively, performed and collected as in the first trial (the only difference being the presence of the therapist through videoconferencing for one of the trials). The third trial of the 6MST will be followed by a semistructured interview using a guide created a priori. This interview will focus on the 2 themes, that are (1) level of comfort executing the test (ease of execution, symptoms, and anxiety) and (2) perception of safety (regarding test and home and telerehabilitation settings). The interview will be conducted in person or through videoconferencing software, depending on the randomization of the third trial.

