### Data Preparation and Analysis

All data will be stored in digital databases (REDCap [Research Electronic Data Capture] in Québec and OpenClinica in France) on secured servers at the participating research facilities (CR-IUCPQ and GHICL) following local protocols. Using a standardized thesaurus, research teams will enter data directly into both databases through remote access. With regard to data analysis, descriptive statistics will be used to summarize participant characteristics. For quantitative data, normality will be verified with Shapiro-Wilk tests and Q-Q plots. All statistical analyses will be completed using SPSS Statistics Version 28 (IBM) with a significance level set at *P*<.05. Graphical analyses will be conducted using Excel (version 2305; Microsoft Corporation) and qualitative analyses will be performed with Nvivio (version 14; Lumivero).

For objective 1, concurrent validity will be assessed using paired sample *t* tests (or Wilcoxon signed-rank tests) to verify whether peak cardiorespiratory (eg, oxygen consumption, minute ventilation, and heart rate) and symptomology (ie, dyspnea and leg fatigue) values obtained during the 6MST are comparable to the CPET and 6MWT. Pearson correlation coefficients (*r*) will also be calculated to quantify the strength of association between peak cardiorespiratory and symptomology values reached during the 6MST with those reached during the CPET and the 6MWT. Additional Pearson correlation coefficients (*r*) will be calculated to determine the strength of the association between the number of steps taken during the 6MST and peak oxygen consumption and heart rate reached during all 3 tests. The level of correlation will be interpreted as poor (≤0.20), fair (0.21-0.40), moderate (0.41-0.60), good (0.61-0.80), and very good (0.81-1.00) [41]. The agreement will be assessed with Bland-Altman plots and 95% limits of agreement (mean difference ± 1.96 SD of the difference) between peak cardiorespiratory and symptomology values reached during the 6MST and those reached during the CPET and the 6MWT [41].

For objective 2, reliability (trial 2 vs 3) will be assessed using paired sample *t* tests (or Wilcoxon signed-rank tests), Bland-Altman plots (with 95% limits of agreement), and intraclass correlations [42-44]. Intraclass correlations will be interpreted as poor (≤0.50), moderate (0.51-0.75), good (0.76-0.9), and very good (0.91-1.00) [44].

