### Strengths and Limitations

This research project has strengths and limitations that warrant consideration. With regard to strengths, first, sex parity will be assured and help limit bias, particularly related to the under-representation of people of the female sex in the pulmonary rehabilitation literature [46]. Second, the a priori calculation of sample sizes required will ensure sufficient statistical power to address the study’s objectives. Third, the inclusion of several different and complementary statistical strategies will ensure adequate evaluation of the metrological properties of the included tests. Fourth, the multicenter and multinational nature of this study will improve its external validity and generalizability. Fifth, the inclusion of a mixed methods study design will help ensure that stakeholders (ie, individuals with pulmonary diseases) have input regarding the acceptability and use of the physical tests being validated in this research project. Finally, the publication of this protocol a priori will ensure accountability and any changes made a posteriori will be public knowledge and require justification.

With regard to limitations, first, only individuals with COPD and an ILD will be included in this study. This will limit its generalizability in the population with other pulmonary diseases (eg, asthma and cystic fibrosis). This methodological choice was made in an effort to reconcile feasibility (limited time and budget) and generalizability (ie, heterogeneity). Second, for study 1, participants will be required to perform several physical tests on the same day, potentially leading to fatigue that may alter performances. To address this, tests occurring on the same day are separated by a rest period and are randomized. Moreover, the research team has extensive experience with this type of protocol. Finally, regarding test-retest reliability in study 2, a learning effect is possible as the test will be conducted repeatedly. To limit this effect, the first trial of the test will exclusively serve as a familiarization trial. In addition, a 2-minute warm-up period is allotted before each trial. Nonetheless, as the learning effect may not be completely eliminated, randomization of the second and third trials is performed in order to limit a systemic effect on the test conditions (ie, with a therapist present or through videoconferencing software).

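### Objective 2 pairs trial 2 with trial 3, but supervision mode is randomised across those trials, so the mean difference as written estimates order, not direct versus remote

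*Protocol article*

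**What the plan says.** Study 2 has a familiarisation trial followed by two test trials. The section Second and Third Trials sets the design as follows: "The second and third trials of the 6MST will be performed in a randomized order, with either direct (therapist present at the home) or remote" (by videoconference). Each participant therefore has one trial per mode, and the position of each mode is random.

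The objective is framed by mode: "Objective 2 is to determine test-retest reliability for the 6MST in home-based settings under direct and remote (ie, videoconferencing) monitoring". The hypothesis is that "measurement error will be minimal and intraclass correlations will be good and similar between direct and remote supervision". Strengths and Limitations gives the reason for randomising: "randomization of the second and third trials is performed in order to limit a systemic effect on the test conditions", so that any remaining learning does not fall on one condition.

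The analysis is framed by trial number. Data Preparation and Analysis has "For objective 2, reliability (trial 2 vs 3) will be assessed using paired sample" t tests or Wilcoxon tests, Bland-Altman plots with 95% limits, and ICCs. The abstract agrees: "intraclass correlations will be used to compare trials 2 and 3". No section states a direct-versus-remote contrast for objective 2.

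**The concern.** If trial 2 and trial 3 are positions in time, each holds a mixture of direct and remote tests. Trial 3 minus trial 2 is then remote minus direct in one sequence and direct minus remote in the other. Averaged over both sequences, a mode effect enters with opposite signs and drops out, leaving whatever learning remains after familiarisation.

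At stake is the signed direct-remote bias. A systematic shift in step count under videoconference supervision could be reported as a mean difference near zero. The random order was introduced to keep the comparison of conditions fair, yet the analysis as worded does not make that comparison.

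**Working it through.** **Inputs from the article.** N = 52 for study 2; minimum and expected ICC 0.50 and 0.75; power 80%; α .05; dropout 15%; one direct and one remote trial per participant in random order. For scale, the Background cites a threshold "with a minimally important difference estimated at 40 steps", given for COPD after rehabilitation.

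**Inputs assumed.** Balanced order (22 per sequence); SD of within-person differences between 40 and 82 steps. The upper end follows from an assumed between-person SD of 100 steps with the article's expected ICC of 0.75: 100 × √(2 × 0.25/0.75) ≈ 82.

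**The article's own sample size.** The usual ICC formula with k = 2 trials is n = 1 + 2k(z_α + z_β)² / [(k − 1)(ln C₀)²], where C₀ = [1 + kρ₀/(1 − ρ₀)] / [1 + kρ₁/(1 − ρ₁)] = 3/7. Two-sided α gives n = 44.7, so 45. Then 45 × 1.15 = 51.75, so 52 (45/0.85 gives 53). The figure of 52 reproduces and is not in question. Completers: 52 × 0.85 ≈ 44.

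**The contrast.** Let δ be remote minus direct, π the order effect (trial 3 minus trial 2 within a mode), and p the share with remote third.

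- Remote third: E[T3 − T2] = π + δ
- Direct third: E[T3 − T2] = π − δ
- Overall: E[T3 − T2] = π + δ(2p − 1)

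At p = 0.5 the δ term is exactly zero, whatever the SD. With a 24/20 split, 2p − 1 = 4/44 ≈ 0.09, so a 40-step bias would leak in as about 3.6 steps, mixed with π.

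**What the mode effect does instead.** It adds spread: SD(T3 − T2) ≈ √(SD² + δ²).

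- SD 40, δ = 40: √(1600 + 1600) ≈ 57; limits widen from ±78 (1.96 × 40) to ±111.
- SD 82, δ = 40: √(6724 + 1600) ≈ 91; limits widen from ±161 to ±179. The one-way ICC falls from 0.75 to about 0.70.

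**Rejection rates** (44 completers, no order effect, two-sided .05):

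| SD of differences | True mode bias | Trial 2 vs 3 rejects | Paired by mode rejects |
|---|---|---|---|
| 40 | 40 steps | 0.6% | about 100% |
| 82 | 40 steps | about 3% | about 89% |
| 40 | 20 steps | 3% | about 90% |
| 60 | 20 steps | about 4% | about 58% |
| 82 | 20 steps | about 4% | about 36% |

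The trial 2 vs 3 rate falls below 5% because the mean is zero while the SD is inflated.

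**Order and mode together.** At SD about 82, with δ = −40 and π = +20, simulated trial 3 minus trial 2 averages +20.1 (the order effect) and remote minus direct averages −39.8 (the mode effect). The same data answer both questions, depending on the pairing.

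**The case against.** **The labels may mean the conditions.** Trials numbered by time cannot themselves be put in random order, so phrases about randomising the second and third trials suggest that the labels stand for direct and remote. The abstract introduces the two trials as one under each form of supervision and then compares them. This reading is plausible. But Table 2 lists trials 1, 2 and 3 in sequence, the interview follows the third trial, and its format depends on which mode was randomised to that trial. Trial 3 is therefore remote for some participants and direct for others. The text supports both readings, and an analyst following it literally would compute the order effect.

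**The objective is reliability, not a mean difference.** Also fair. Study 2 is sized on the ICC, and a shift between successive trials is a proper part of test-retest work. A one-way ICC does not depend on labels within a pair, so it takes in a mode effect, as do the limits of agreement. A reader might infer that the whole reliability assessment fails, or that a mode effect would leave no trace. The documents do not support that: the ICC would fall and the limits would widen. Neither output, however, gives the direction of a mode bias or separates it from random error. Every trial 2/3 pair also crosses modes, so none is a retest under the same supervision.

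**The magnitude is assumed.** The article gives no SD of differences, which is why a range is shown, and the power of the corrected pairing varies widely over it. The 40-step threshold comes from COPD, whereas the sample is half ILD. The cancellation itself depends on neither figure.

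**A period term is analysis-plan detail.** Agreed; its absence from an article is no fault. The point is the contrast that the article states.

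**Conclusion.** The point holds as an error in the stated contrast, and it is limited to the paired test and the Bland-Altman mean. Taken literally and with balanced order, these estimate residual learning, and the signed direct-remote bias is not estimated. A 40-step mode bias would give a mean near zero and reject in about 0.6% to 3% of studies, against about 100% to 89% when paired by mode. These figures assume 44 completers, 22 per sequence, and SDs of 40 to 82 steps; the cancellation needs only balanced order.

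A reader might go further and conclude that the authors certainly chose the wrong comparison, or that estimating a mean mode effect is the declared purpose of study 2. Neither follows: the shorthand reading is open, and the stated objective is test-retest reliability with a hypothesis of similarity between modes. The sample size, the random order and the planned data are sound for the corrected analysis.

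**What to change.** In Data Preparation and Analysis and in the abstract, replace the trial 2 vs 3 wording for objective 2 with a paired difference defined as remote minus direct. Use it for the t test (or Wilcoxon) and the Bland-Altman plot, and report the mean with a 95% CI.

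Preferably take that estimate from the two-period crossover model, with mode and period as fixed effects and participant as random. With exactly balanced order the simple paired difference is already unbiased. The model additionally removes the order effect from the error and copes with unequal sequences after dropout.

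Report trial 3 minus trial 2 separately, labelled as the order (learning) effect.

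The cost is a change of wording. N stays at 52, and mode and order are known for every trial, so no new data are needed. The article plans study 2 recruitment after study 1 and undertakes to justify later changes publicly. The correction is best recorded before any study 2 results are seen, since re-pairing afterwards would look post hoc.

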### Ethical Considerations

This research project received ethical approval at the CR-IUCPQ on October 12, 2023 (2024-4075, 22380), and at the GHICL on September 25, 2023 (2023-A01571-44). All participants will provide written free and informed consent before enrollment. All information is provided in French and will be translated into English if needed. All data collected will be stored anonymously (coded numeric ID) on secured servers at participating research facilities. Participants will receive financial compensation in accordance with local standardized fees in participating research centers (value of approximately CAD $40[US $30] per laboratory visit and CAD $10 [US $7] per at-home visit).

## Results

The first participant (study 1) was recruited on February 2, 2024, and will continue for a maximum of 12 months. Recruitment for study 2 is to follow the completion of study 1 and is expected to last for a maximum of 12 months. Data analysis will occur after, and results will be published in peer-reviewed journals.

## Discussion

### Overview

This study aims to provide further evidence regarding the metrological properties of the 6MST in individuals with COPD or ILD. The 6MST is a clinically relevant functional capacity test that is specifically adapted for home-based models of care.

This research project innovates by being among the first to extensively evaluate the metrological properties of the 6MST in a diversified sample of pulmonary lung diseases. Moreover, this study is the first to evaluate the validity and safety of assessing exercise capacity using 6MST through direct and remote monitoring, mimicking home-based and telerehabilitation contexts. Since all the equipment required for the 6MST (ie, stepper) can easily be transported by a therapist, or even shipped to the patient, and requires very minimal space, this test is highly applicable in home-based rehabilitation models of care.

Knowledge derived from this research project will therefore contribute to addressing barriers currently hampering the wider adoption of these new models of care. Ultimately, this research project fits in a continuum of knowledge creation that aligns with the United Nations Sustainable Development Goals by contributing to augmenting health care service delivery (goal 3) and reducing health care access inequalities (goal 11).

### Potential Challenges and Appropriate Mitigation Strategies

Certain potential changes were foreseen and the following mediation strategies will be put into place:

Changes in a participant’s health status during the study could introduce bias in the results of repeated measures. To help reduce this risk, repeated testing conducted in the laboratory will be preceded by spirometry to ensure stability in health status. For testing conducted in the home-based settings, signs and symptoms of exacerbations will be collected before each repeated testing.The steppers used in this study use hydraulic pistons to simulate the stepping movements. The resistance provided by the pistons is greater when the fluid inside them is cold and decreases progressively with use as the pistons heat. To avoid inducing a potential bias during repeated tests, a standardized 2-minute warm-up (familiarization) will be conducted followed by a standardized 3 minutes of rest before initiating the test trial. Participants will also be instructed not to use the stepper device other than when instructed to do so during testing.Some participants may have trouble maintaining balance during the 6MST. Participants are allowed to touch a wall or other stable surface to assist in maintaining balance. Nevertheless, for home-based testing in the absence of the therapist (ie, videoconferencing), a third person (eg, family member) will be present to ensure safety. This person will also be instructed on how to react in case of emergency.

### Strengths and Limitations

This research project has strengths and limitations that warrant consideration. With regard to strengths, first, sex parity will be assured and help limit bias, particularly related to the under-representation of people of the female sex in the pulmonary rehabilitation literature [46]. Second, the a priori calculation of sample sizes required will ensure sufficient statistical power to address the study’s objectives. Third, the inclusion of several different and complementary statistical strategies will ensure adequate evaluation of the metrological properties of the included tests. Fourth, the multicenter and multinational nature of this study will improve its external validity and generalizability. Fifth, the inclusion of a mixed methods study design will help ensure that stakeholders (ie, individuals with pulmonary diseases) have input regarding the acceptability and use of the physical tests being validated in this research project. Finally, the publication of this protocol a priori will ensure accountability and any changes made a posteriori will be public knowledge and require justification.

With regard to limitations, first, only individuals with COPD and an ILD will be included in this study. This will limit its generalizability in the population with other pulmonary diseases (eg, asthma and cystic fibrosis). This methodological choice was made in an effort to reconcile feasibility (limited time and budget) and generalizability (ie, heterogeneity). Second, for study 1, participants will be required to perform several physical tests on the same day, potentially leading to fatigue that may alter performances. To address this, tests occurring on the same day are separated by a rest period and are randomized. Moreover, the research team has extensive experience with this type of protocol. Finally, regarding test-retest reliability in study 2, a learning effect is possible as the test will be conducted repeatedly. To limit this effect, the first trial of the test will exclusively serve as a familiarization trial. In addition, a 2-minute warm-up period is allotted before each trial. Nonetheless, as the learning effect may not be completely eliminated, randomization of the second and third trials is performed in order to limit a systemic effect on the test conditions (ie, with a therapist present or through videoconferencing software).

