**Exclusion criteria**
Interstitial lung disease associated with connective tissue disease and sarcoidosis (often accompanied by multisystemic effects)Unstable or severe cardiac conditionInvalidating rheumatologic or neurologic conditionWeight exceeding maximal limits of exercise equipment (eg, 130 kg for the stepper)Any other physical or medical condition limiting or contraindicating exercise testingSimultaneous participation in another study requiring changes in medicationRecent pulmonary rehabilitation (≤1 year, potential learning bias for the 6-minute walk test and the 6-minute stepper test)For study 1 only: use of oxygen therapy (unable to provide oxygen therapy during testing due to limitation of gas exchange analysis equipment)For study 2 only: participation in study 1

For study 1, a mean difference of 0.28±0.32 L/min in maximal oxygen uptake between the 6MST and CPET was assumed, based on previous studies between the 6MWT and CPET [22,24]. To detect a difference of this amplitude with a paired sample *t* test, assuming a power of 80%, an α level of .05, and a dropout rate of 15%, 15 participants are needed. Fifteen individuals of each disease population (ie, COPD, n=15; ILD, n=15) will be included for a total sample of 30 participants (Québec, n=15; France, n=15), as cardiorespiratory responses to exercise are different among these populations [25].

For study 2, a minimal acceptable intraclass correlation coefficient of 0.5, and an expected intraclass correlation coefficient of 0.75, were assumed for the test-retest reliability of the 6MST. Assuming a power of 80%, an α level of .05, and a dropout rate of 15%, 52 participants (Québec, n=26; France; n=26) will be recruited. This calculated sample was taken as a whole, as test-retest reliability is not expected to be influenced by the type of respiratory disease.

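### The claim of sufficient power for the study's objectives goes beyond the calculation: study 1's Pearson correlations, limits of agreement and similarity to the 6MWT were never sized

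*Protocol article*

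**What the plan says.** Strengths and Limitations lists as a strength that "the a priori calculation of sample sizes required will ensure sufficient statistical power to address" the study's objectives, without restriction to particular analyses.

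The calculation is in Participants and Inclusion and Exclusion Criteria. For study 1, "a mean difference of 0.28±0.32 L/min in maximal oxygen uptake between the 6MST and CPET was assumed". The test is named: "To detect a difference of this amplitude with a paired sample" t test. The result is given as "assuming a power of 80%, an α level of .05, and a dropout rate of 15%, 15 participants are needed". This is applied to each disease: "Fifteen individuals of each disease population (ie, COPD, n=15; ILD, n=15) will be included for a total sample of 30 participants". For study 2, an intraclass correlation of 0.75 is set against a minimum of 0.5, which gives 52 participants taken as one group.

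Objective 1 (Objectives and Hypotheses) is wider than the study 1 calculation. It expects peak responses and symptoms in the 6MST to correlate strongly with those in CPET and in the 6MWT, to be lower than in CPET, and to be similar to those in the 6MWT. Data Preparation and Analysis assigns paired t tests, Pearson correlations and Bland-Altman limits of agreement to this objective. It adds further correlations between "the number of steps taken during the 6MST and peak oxygen consumption and heart rate reached during all 3 tests". The coefficients are to be labelled poor, fair, moderate, good or very good.

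**The concern.** A sample size that detects a mean difference of 0.28 L/min says nothing about power for a correlation, about the precision of limits of agreement, or about the ability to show that two tests give similar values. The article nevertheless presents its calculation as securing power for the objectives as a whole.

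A reader who relies on that sentence could take a weak or non-significant correlation as evidence against validity when the sample was too small to tell. The same reader could take a verbal band such as good at face value when the interval around r covers several bands.

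**Working it through.** **1. Reproducing the stated sizes (two-sided α of .05, the only sidedness that recovers both figures).**

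Study 1: standardised difference = 0.28/0.32 = 0.875. The noncentral t distribution gives a paired t test 78.8% power with 12 completers and 82.5% with 13, so 13 are needed. 13 × 1.15 = 14.95, giving the stated 15. Dividing instead, 13/0.85 = 15.3, giving 16.

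Study 2 (two trials): C = [1 + 2(0.5)/0.5] / [1 + 2(0.75)/0.25] = 3/7, so ln C = −0.847. Then n = 1 + 2(1.960 + 0.842)² × 2 / 0.847² = 44.7, so 45. 45 × 1.15 = 51.75, giving the stated 52. Dividing instead, 45/0.85 = 52.9, giving 53.

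Both stated figures are recovered.

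**2. What is sized.**

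| Analysis | Sized? |
|---|---|
| 6MST-CPET mean difference in oxygen uptake, per disease | Yes, 15 each |
| Intraclass correlation, trial 2 vs trial 3, pooled | Yes, 52 |
| Pearson r of peak responses and symptoms, 6MST vs CPET and vs 6MWT | No |
| Additional Pearson r, steps vs peak oxygen consumption and heart rate | No |
| Bland-Altman limits of agreement in study 1 | No |
| Similarity of 6MST and 6MWT responses | No |

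**3. Power of a Pearson correlation against r=0.** Two-sided .05, bivariate normal data, by simulation of the t test for r. Sizes are 13 (completers needed) and 15 (recruited) per disease, and 30 if the diseases are pooled.

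| True r | Source in the article | n=13 | n=15 | n=30 |
|---|---|---|---|---|
| 0.39 | Background: steps "and peak oxygen consumption during CPET" in COPD | 27% | 31% | 59% |
| 0.61 | Lower bound of the good band | 65% | 72% | 96% |
| 0.70 | Background: steps vs 6MWT distance in ILD, used here as an example of a strong correlation | 82% | 88% | over 99% |

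The Fisher z approximation is slightly lower: 26%, 30% and 57% in the first row. By the same approximation, n = [(1.960 + 0.842)/atanh(r)]² + 3. For 80% power this gives 50 participants at r=0.39 and 19 at r=0.61.

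**4. Precision of r.** With 13 completers and an observed r of 0.70, atanh(0.70) = 0.867 and SE = 1/√10 = 0.316. The 95% interval on the z scale is 0.867 ± 0.620, which transforms back to 0.24 to 0.90. On the article's scale that runs from fair to very good.

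**5. Precision of the limits of agreement.** With the planning SD of 0.32 L/min, the limits are 0.28 ± 1.96 × 0.32, or about −0.35 to 0.91 L/min. The SE of each limit is 0.32 × √[1/n + 1.96²/(2(n−1))].
- n=13: SE 0.156; × t(12) of 2.179 = ±0.34 L/min.
- n=15: SE 0.144; × t(14) of 2.145 = ±0.31 L/min.

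**6. Dropout.** At the stated sizes, 15% loss leaves 12.75 expected completers per disease and 44.2 in study 2. Averaged over binomial dropout, power is 81.0% in study 1 and 79.4% in study 2.

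**The case against.** Several counter-arguments carry weight.

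- A central Objective 1 analysis was sized. The article assesses concurrent validity first with paired t tests, and the expected shortfall against CPET is exactly the difference in the calculation. Sizing a study on one main comparison is ordinary practice. This stands, but it justifies a narrower statement than the one made.
- A reader might infer from r=0.39 that the main validity correlations have about 30% power. The article does not support that. The figure belongs to steps against peak oxygen consumption, which is planned only as an additional correlation. The main hypothesis concerns the same response across tests and expects a strong association, and no prior r is given for it. At a true r of 0.70 power is adequate even per disease.
- The article does not say whether the correlations will be run per disease or pooled. Pooling gives 96% power at r=0.61. It leaves the r=0.39 case short, and it sits uneasily with the stated reason for sizing the diseases separately, that their responses differ.
- Correlations and limits of agreement are estimates, so power against zero is an incomplete yardstick. That favours stating their precision over claiming power. How intervals are reported may properly be left to a fuller document; the error here is the affirmative power claim.
- A reader might also infer that 80% power is lost after dropout, because both sizes fit multiplication by 1.15. The article does not say how the 15% was applied. The stated sizes are one participant below division by 0.85 (15 vs 16, 52 vs 53). Average power stays at about 81% and 79%, so the difference is not material.

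**Conclusion.** The point holds as an overstatement of what the calculation secures. The article supports 80% power for two tests only: the 6MST-CPET oxygen uptake difference within each disease, and the pooled intraclass correlation of 0.75 against 0.5. Study 1's Pearson correlations, limits of agreement and similarity to the 6MWT have no sample size behind them.

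The consequence depends on the true correlation. Per disease, power is adequate near r=0.70, short at the floor of the good band, and low for the additional steps correlation at r=0.39. Whatever the true value, 13 to 15 participants leave both r and the limits of agreement imprecise.

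Assumptions: two-sided testing, per-disease analysis in study 1 (with pooled figures shown), bivariate normal data, and the planning SD of 0.32 L/min. The stated sample sizes themselves reproduce, and no fault is found with them.

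**What to change.** In Strengths and Limitations, and where the sizes are derived in Participants and Inclusion and Exclusion Criteria, limit the power statement to the two sized tests. State there that study 1's correlations and limits of agreement are estimates, and that the similarity hypothesis for the 6MWT was not sized.

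In Data Preparation and Analysis, report a 95% CI with every r and every limit of agreement, and apply the strength bands to r only together with its interval.

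The cost is a less favourable power statement and a few added intervals. Enrolment, procedures and planned tests do not change, and the dropout allowance can stay as it is.
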